[62. Name and role of research allotment person, etc. 22](#_Toc122877524)

[63. Research Secretariat, Statistical Analysis 22](#_Toc122877525)

[64. Joint Research Institutes 22](#_Toc122877526)

[65. Contact point for inquiries about research 22](#_Toc122877527)

[66. References 22](#_Toc122877528)

Abstract

- 1. **Schema**

Eligibility

Healthy adults

Aged between 20 and 64 years-old

Both males and females

MoCA-J ≧26

Standard blood test and urine test

Body measurements, grasping power of both the hands, two-step test, and functional reach test

Wechsler Memory Scale-Revised, digit span, tapping span, Stroop Color Test, and Trail Making Test

T1-weighted MRI and rs-fMRI

24w

D 0

Placebo

GBE

GBE/MST

- 1. **Purpose**

Ginkgo biloba extract (GBE) is available in the form of health supplements in Japan, with claims of ameliorating memory and attention and mitigating the symptoms of Alzheimer’s disease. However, its efficacy in the cognitive function of healthy adults remains controversial. It was reported that concentrations of terpene lactones, active components of GBE that are present in very low concentrations in the brain, were significantly increased following administration of a mixture of GBE, sesame extract, and turmeric oil (GBE/MST) in mice. This study aims to investigate the effectiveness of GBE/MST on the cognitive function of healthy adults. For biological assessment, resting state functional magnetic resonance imaging (rs-fMRI) will be performed simultaneously with the neuropsychological tests.

- 1. **Subjects**

１）Inclusion criteria

- Male and female participants aged between 20 and 64 years
- Normal cognitive function at baseline, confirmed by the Japanese version of the Montreal Cognitive Assessment battery (MoCA-J) (score ≧26)

２）Exclusion criteria

1. History of severe neurological diseases
2. History of critical bleeding incidents
3. Use of antithrombotic medications
4. Severe depression
5. Diabetes mellitus
6. Severe visual or auditory disability
7. Metal implantation such as cardiac pacemaker, coronary stent, and artificial joints
8. Claustrophobia
9. Use of any supplements
10. Creatinine clearance below 15 mL/min
11. Gastrointestinal diseases or metabolic diseases
12. Diagnosed psychiatric disorders
13. Participants who cannot provide informed consent
14. Allergy to the study materials
15. Individuals not suitable for participation by the decision of the principal investigator
    1. **Sample size and period**
16. Sample size：159（control 53、GBE only 53、GBE/MST 53）、randomized, double-blind
17. Study period：April 2021（post ethical approval）～December 2022

（registration：～February 2022、follow up：～August 2022）

# Porpose

This study aims to investigate the effectiveness of a mixture of Ginkgo biloba extract (GBE), sesame extract, and turmeric oil (GBE/MST) on the cognitive function of healthy adults.

# Backgrounds and study rationale

# Backgrounds

GBE is available in the form of health supplements in Japan and the USA, with claims of ameliorating memory and attention and mitigating the symptoms of Alzheimer’s disease. However, its efficacy in the cognitive function of healthy adults remains controversial. No effect was reported on memory enhancement and on the intelligence test scores after 6 days of GBE administration in healthy adults aged 20 years [1]. Reportedly, healthy elderly individuals showed no improvement in memory but showed improvements in executive functions after 6 weeks of GBE administration [2]. There was no difference in the prevalence rate of cognitive decline between the GBE and placebo groups for 42 months among healthy adults aged over 85 years. However, among participants who maintained good adherence throughout the study period, GBE was associated with a significantly reduced rate of cognitive decline when compared with placebo [3].

GBE has two active components, flavonoids and terpene lactones. Flavonoids have been reported to accumulate in the blood serum [4]. Since major effects of flavonoids include reduction in the inflammatory response, oxidization, and platelet aggregation in vivo, these effects are expected to play important roles in inhibiting damage to the vascular endothelial cells and improving the peripheral blood flow [5]. Terpene lactones have been reported to infiltrate the central nervous system (CNS) but are quickly metabolized, resulting in very low concentrations in the CNS [4]. Since terpene lactones were reported to reduce caspase-3 activation and amyloid-β aggregation and protect the mitochondrial membrane, they can be expected to protect the neurons from apoptosis and amyloid-β toxicity [6]. However, since the concentration of terpene lactones in the CNS might be very low in vivo [4, 7], the effect of GBE on cognitive function may be exclusively explained by improvement in the cerebral blood flow. Administration of a mixture of GBE, sesame seed extract, and turmeric oil (GBE/MST) was reported to increase the concentration of terpene lactones in the mouse brain [7]. The aforementioned study reported that the concentration of bilobalide, a terpene lactone, in the brain was not significantly different between the GBE alone and GBE/MST groups (mean ± standard error of the mean: 1.30±0.31 and 0.75±0.24 μg/mg, respectively). Ginkgolide A, another terpene lactone, was detected in the GBE/MST group, but it was not detected in the GBE alone group. The GBE/MST supplement is currently available in the Japanese market, although its scientific effects have not been validated. Since low bioavailability of GBE in the brain may be a possible cause of its faint effect on the cognitive function, it might be of great interest to investigate whether the efficacy of GBE is improved by administration in the form of GBE/MST in healthy adults.

# Scientific rationale

According to a meta-analysis involving nine clinical studies [8], a significant improvement was observed in the Syndrome-Kurztest scores following GBE administration in patients with Alzheimer’s disease. There was no significant difference in Alzheimer’s Disease Assessment Scale-Cognitive Subscale scores between patients consuming GBE and those consuming placebo. However, this difference was greater among patients consuming GBE in a dose of 240 mg/day compared to those on a dose of 120 mg/day. The difference was also greater in the observation period of 22-24 weeks compared to a period of 12 weeks. There was no difference in the adverse incident rate between GBE dose of 120 mg/day and 240 mg/day. Moreover, there was no difference in the dropout rate due to adverse effects between GBE doses of 120-160 mg/day or 240 mg/day and placebo [8, 9].

# Study design

# Study population

A population is healthy adults.

# Inclusion criteria

1. Male and female participants aged between 20 and 64 years at baseline
2. With informed consent
3. Normal cognitive function at baseline, confirmed by the Japanese version of the Montreal Cognitive Assessment battery (MoCA-J) (score≧26)

# Exclusion criteria

1. History of severe neurological diseases
2. History of critical bleeding incidents
3. Use of antithrombotic medications
4. Severe depression
5. Diabetes mellitus
6. Severe visual or auditory disability
7. Metal implantation such as cardiac pacemaker, coronary stent, and artificial joints
8. Claustrophobia
9. Use of any supplements
10. Creatinine clearance below 15 mL/min
11. Gastrointestinal diseases or metabolic diseases
12. Diagnosed psychiatric disorders
13. Participants who cannot provide informed consent
14. Allergy to the study materials
15. Individuals not suitable for participation by the decision of the principal investigator

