# Rationale

The primary endpoint of this study is to determine the impact of GBE/MST on cognitive function in healthy adults, which will be assessed by the Wechsler Memory Scale-Revised (WMS-R) after 24 weeks of GBE/MST administration. The WMS-R is designed to indicate a standard deviation of 15 if its normal average score is 100. In the present study, when the estimated alteration rate of the standard deviation was 1%, the difference in the average score was 6. Cohen’s calculation formula with an effect size of 0.4 at a significance level (α) of 0.05 and a detection power (1-β) of 80% yielded a sample size of 44 participants. Considering a dropout rate of 20%, 159 participants will be required (53 participants in each group).

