Standard blood and urine tests will be performed to check for health status. Body measurements, grasping power of both the hands, two-step test, and functional reach test will be performed at baseline and at the endpoint (24 weeks).

Cognitive tests will be completed by the participants at baseline and at the endpoint. The WMS-R and its lower domains will be used to measure total memory function and assess individual function (digit span indicates verbal memory and the tapping span indicates visual memory). Stroop Color and Word Test and Trail Making Test will be employed to assess executive functions such as restraint-related functions and sustained attention, respectively.

Magnetic resonance imaging (MRI: Achieva Intera 3T, Philips Healthcare, Quasar Dual, The Netherlands) will be performed at baseline and at the endpoint. T1 weighted magnetization-prepared rapid acquisition gradient echo (MPRAGE) structural images (matrix: 240 × 240, repetition time: 8.70 ms, echo time: 3.1 ms, flip angle: 8°, field of view: 256 × 256 × 180 mm, 162 slices, voxel size: 0.7 × 0.7 × 0.7 mm, and scan duration: 5 min 15 s) will be acquired to collect 3D structural datasets. Resting state functional MRI (rs-fMRI: T2*-weighted gradient-echo planar imaging, matrix: 64× 64, repetition time: 3000 ms, echo time: 30 ms, flip angle: 90°, field of view: 220 × 220 ×218 mm, 34 slices, voxel size: 3.44 × 3.44 × 3.40 mm and 197 volumes with 5 min superimposition) with closed eyes will be performed to analyze the DMN.

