**^2)^ Definition of seriousness**

| ① to be fatal  ② life-threatening  ③ to need in-patient treatment or extension of hospitalization   1. to be a permanent or salient disability / incapacity 2. inducing congenital abnormality in offsprings |
| --- |

Excluding events: hospitalization appointed by the study procedure, hospitalization for a therapy or an examination scheduled prior to the study registration, and hospitalization except for a treatment / examination of adverse events.

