# Description of adverse events

Investigators etc. must describe in the CRF about name, severity (seriousness, non-seriousness), reason of desiding seriousness, date of onset and prognosis, treatment, outcome (recovered, remission, recovered with sequera, not recovered, or death), relationship with the relevant medicine/appalatus, comments (causality and reason of decision) regarding all adverse events.

- 1. The name of adverse event must be written with diagnosis name/ disease name in the CRF. If diagnosis name/ disease name can not be specified or investigators etc. decide appropriate not to describe diagnosis name/ disease name, clinical condition or symptoms (including abnormal lab data) can be alternatively written in the CRF.
  2. Describe the treatments (yes/no) for adverse events of the participant.

③ Describe the outcome of adverse events.

| **Outcome** | **Description** |
| --- | --- |
| Recovered | The adverse event is eliminated, or it returns to original. |
| Remission | Although the adverse event is not completely recovered, it is almost eliminated or returns to almost original. |
| Recovered with sequera | Although the adverse event is returned to original, a sequera remains. |
| Not recovered | The adverse event is ongoing. |
| Death | The adverse event causes death. |

Definition of adverse events:

All undesirable or unexpected diseases and injury or symptoms (including lab data abnormality) regardless of causality to the study. Collection of adverse events will be performed from registration to the end or termination of observation of each participant.

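### No named criterion or screening step addresses pregnancy or breastfeeding, and adverse event collection of about 24 weeks would miss many offspring outcomes that the protocol classes as serious

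*Protocol*

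**What the plan says.** Protocol, Inclusion criteria: "Male and female participants aged between 20 and 64 years at baseline". The other two requirements are consent and a MoCA-J score of at least 26.

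Protocol, Exclusion criteria, and the matching list under Subjects in the Abstract: 15 items, identical in both places. None mentions pregnancy, breastfeeding, planned pregnancy or contraception. The last item is "Individuals not suitable for participation by the decision of the principal investigator".

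Protocol, Methods (Schedule): "Standard blood and urine tests will be performed to check for health status". No pregnancy check is named.

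Protocol, Sample size and rationale (Rationale): the primary assessment comes "after 24 weeks of GBE/MST administration".

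Protocol, Assessment of adverse events, Definition of seriousness: the last of five categories is "inducing congenital abnormality in offsprings".

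Protocol, Description of adverse events: "Collection of adverse events will be performed from registration to the end or termination of observation of each participant".

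Two other places bear on the window. Response to the adverse event / incident asks investigators to follow an event until it resolves, but allows this to stop at the end of the study. A footnote to the reporting table covers the treatment period and 30 days after the last protocol treatment, for the starred entries only.

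**The concern.** Eligibility belongs in the protocol, and both lists are shown in full, so this is not a matter left to another document. A healthy woman in early pregnancy with a sufficient MoCA-J score meets none of the 14 specific exclusions. The fifteenth allows the principal investigator to exclude her but does not require it, and it cannot act on a pregnancy that nobody is told to ask about. The risk section does direct staff to ask about tape reactions, alcohol allergy, vasovagal episodes and internal metal, so an entry question on pregnancy would fit existing practice.

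Participant protection is what is at stake. Two of the three arms, 53 + 53 = 106 of 159 participants, are to take ginkgo extract for 24 weeks. If a participant is or becomes pregnant, the protocol does not say that the pregnancy is recorded or its outcome sought, although an affected offspring would meet its own definition of a serious event.

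**Working it through.** The protocol gives no figure to reproduce here. The only arithmetic is whether a birth falls inside the collection window.

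**Inputs**
- Observation after entry: 24 weeks (Rationale; Methods). The protocol puts no number on the end of observation. The 24-week endpoint assessment is taken as the end.
- Reporting footnote: 30 days = 30/7 = 4.3 weeks after the last treatment, for starred entries only.
- Gestational age at birth: 40 weeks, range 37 to 42. This is an assumption and is not in the protocol.
- Gestational age at conception: 2 weeks, by the usual dating convention (assumption).

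**Conception during the trial.** The earliest case is conception on day 0.
- Gestational age at the last visit: 2 + 24 = 26 weeks.
- With the 30-day footnote: 26 + 4.3 = 30.3 weeks.
- Shortfall against the earliest term birth in the range: 37 − 30.3 = 6.7 weeks. Against 40 weeks: 9.7 weeks.

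A later conception is less advanced at both points, so no term birth from a conception during the trial falls inside either window.

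**Already pregnant at entry.** Birth falls inside the window if gestational age at entry is at least the gestation length minus the window length.

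| Birth at | Minimum at entry, 24 weeks | Minimum at entry, 24 weeks + 30 days |
| --- | --- | --- |
| 37 weeks | 13 weeks | 8.7 weeks |
| 40 weeks | 16 weeks | 11.7 weeks |
| 42 weeks | 18 weeks | 13.7 weeks |

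Pregnancies below these thresholds at entry end after collection has closed. Those at or above them deliver inside it.

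**Does another section close the gap?** Continued follow-up applies to events already recorded. The protocol does not ask for a pregnancy to be recorded, so a healthy pregnancy in progress at week 24 gives that provision nothing to act on.

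**The case against.** The strongest reply is that this is an omission and not a contradiction. The list of serious categories is generic: it classifies events and does not predict fetal harm. A category that rarely arises within the window does not conflict with the window. The protocol also states, in its section on burdens and foreseeable risks, that the safety of ginkgo extract, sesame extract and turmeric oil is established, and item 15 leaves room to exclude a pregnant woman.

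Much of this stands, and it rules out several stronger readings that a reader might reach:

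- *That no congenital abnormality could ever be captured.* Not supported. A woman about 16 weeks pregnant or more at entry would deliver within 24 weeks, and an abnormality diagnosed before birth during observation could be recorded.
- *That the protocol itself calls the product unproven in safety.* The Backgrounds section does describe the marketed mixture with the words "although its scientific effects have not been validated", but the surrounding text is about efficacy on cognition.
- *That the protocol acknowledges a hazard in pregnancy.* It does not. The remark on "reduction in the inflammatory response, oxidization, and platelet aggregation in vivo" describes expected vascular benefits of flavonoids, and bleeding is addressed by exclusions 2 and 3.

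What the reply does not remove is the gap in eligibility. The safety statement is general. It names no population and does not mention pregnancy or breastfeeding. It also covers three ingredients, while the capsule description lists others, including Piper longum extract. It cannot stand in for an eligibility rule, and neither can a discretionary item that no question triggers.

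**Conclusion.** The point holds as a cheap improvement. No named exclusion and no screening step addresses pregnancy or breastfeeding, although women from age 20 may enter a 24-week trial. Separately, collection would miss term births from conceptions during the trial and from pregnancies early at entry: below about 16 weeks (range 13 to 18), or below about 12 weeks (range 9 to 14) where the 30-day footnote applies.

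The thresholds rest on the assumed length of gestation and on observation ending at about 24 weeks. The breastfeeding part rests only on the absence of any criterion; the window arithmetic does not bear on it. The number of participants affected cannot be derived, because the protocol gives neither the sex and age mix nor an expected pregnancy rate. Nothing here changes the sample size or the primary WMS-R analysis.

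**What to change.** 1. Add one named eligibility criterion covering pregnancy, breastfeeding and planned pregnancy during the study, in both the Abstract list and the Exclusion criteria section.
2. Add one interview question at registration so that the criterion is actually checked.
3. Reconcile Description of adverse events with Definition of seriousness: state that any pregnancy starting during the study is recorded and that its outcome is obtained, even if this falls after the participant's last visit.

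How a participant who becomes pregnant is managed stays with the investigator.

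The cost is one line in two lists, one question, and an occasional later contact for an outcome. A few otherwise eligible women would not be enrolled.

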# Sample size and rationale

# Sample size

Estimated sample number: 159（Control 53, GBE 53, GBE/MST 53）

# Rationale

The primary endpoint of this study is to determine the impact of GBE/MST on cognitive function in healthy adults, which will be assessed by the Wechsler Memory Scale-Revised (WMS-R) after 24 weeks of GBE/MST administration. The WMS-R is designed to indicate a standard deviation of 15 if its normal average score is 100. In the present study, when the estimated alteration rate of the standard deviation was 1%, the difference in the average score was 6. Cohen’s calculation formula with an effect size of 0.4 at a significance level (α) of 0.05 and a detection power (1-β) of 80% yielded a sample size of 44 participants. Considering a dropout rate of 20%, 159 participants will be required (53 participants in each group).

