# Statistical analysis

# Statistical methods

(1) Analysis of cognitive function

The average of total WMS-R score at the endpoint will be compared among the GBE/MST, GBE, and placebo groups using one-way analysis of variance (ANOVA) and Tukey's test. The difference between the total score at baseline and at the endpoint will be compared among the three groups using multivariate ANOVA (MANOVA).

(2) Analysis of brain morphology

Total cerebral cortical volume will be calculated from the T1-weighted structural images using the SPM12 software. The average alteration in total volume from baseline to the endpoint will be compared among the three groups. Using the CONN toolbox (https://web.conn-toolbox.org/) implemented in MATLAB, functional connectivity (FC) between two regions of interest (ROIs) within the DMN will be analyzed by means of ROI-to-ROI analysis.

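### 44 per group does not follow from an effect size of 0.4 at 80% power: the power for the stated 6-point difference is about 46%, or 31% with the planned Tukey test

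*Protocol*

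**What the plan says.** All the inputs stand in the Protocol, Sample size and rationale, Rationale:

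- Variability: "The WMS-R is designed to indicate a standard deviation of 15 if its normal average score is 100".
- Target: "when the estimated alteration rate of the standard deviation was 1%, the difference in the average score was 6".
- Effect size and error rate: "with an effect size of 0.4 at a significance level (α) of 0.05".
- Result: "a significance level (α) of 0.05 and a detection power (1-β) of 80% yielded a sample size of 44 participants".

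The same paragraph adds 20% for dropout and arrives at 53 per arm, 159 in all. Since 44 × 1.2 = 52.8, which rounds up to 53, the 44 must be per group.

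Under Statistical methods, the WMS-R total at the endpoint is compared "among the GBE/MST, GBE, and placebo groups using one-way analysis of variance (ANOVA"), followed by Tukey's test. This comparison is not adjusted for baseline. A change from baseline is analysed separately.

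**The concern.** The stated inputs and the stated result belong to different calculations. An effect of 0.4 SD between two groups is a modest one, and detecting it with 80% power takes roughly twice as many people per group as the protocol gives.

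The paragraph is the only quantitative justification of the trial's size. A reader who trusts it will believe that the trial had an 80% chance of detecting a 6-point benefit. If the result is null, that reader will take it as evidence that the supplement does not work, which the data could not show. The Background section calls the efficacy of ginkgo extract in healthy adults controversial, so a misread null result would add to the confusion.

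**Working it through.** **Inputs** (Rationale and Statistical methods): SD 15, difference 6, alpha 0.05, power 80%, three equal groups, endpoint score compared by one-way ANOVA and Tukey's test. The protocol does not state sidedness; two-sided is assumed.

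**1. Effect size.** d = 6/15 = 0.4. This matches the protocol's 0.4 and identifies it as Cohen's d.

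**2. Attempt to reproduce 44.** For two means, n per group = 2(1.960 + 0.842)²/0.4² = 98.1, so 99. The exact t-test needs 100 (power 79.97% at 99). The figure of 44 is not reproduced. Other readings:

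| Reading of 0.4 | Required n |
|---|---|
| d, two groups, one-sided | 78 per group |
| d, paired or one-sample, two-sided | 52 |
| d, paired or one-sample, one-sided | 41 |
| Cohen's f, three-group ANOVA | 22 per group |

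The last reading also contradicts the 6-point target. With one arm apart from two equal arms, f = d√2/3, so f = 0.4 means d = 0.4 × 3/√2 = 0.849, or 12.7 points.

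**3. What the planned analysis needs for 6 points.**

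- Omnibus ANOVA, means 6, 0, 0: f = 0.4 × √2/3 = 0.189, giving 92 per group.
- Omnibus ANOVA, means 6, 3, 0: f = 0.4/√6 = 0.163, giving 122 per group.
- Tukey pairwise comparison: 128 per group.

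**4. Power for 6 points at the protocol's numbers.**

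| Completers per group | t-test | Tukey |
|---|---|---|
| 42 (53 less 20%) | 44.1% | 29.9% |
| 44 (as planned) | 45.8% | 31.4% |
| 53 (no dropout) | 53.2% | 38.2% |

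At 44 per group the Tukey critical value on the t scale is 2.371. The omnibus ANOVA at 44 has 46.8% power (means 6, 0, 0) or 36.3% (means 6, 3, 0).

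**5. What 44 per group can detect.** At 80% power: 0.604 SD = 9.1 points (t-test) or 0.686 SD = 10.3 points (Tukey). As a cross-check, 2(2.802)²/0.6² = 43.6, so 44 is roughly the answer for d = 0.6, a 9-point difference.

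**6. Precision.** The standard error of a pairwise difference is 15√(2/44) = 3.20. The 95% half-width is 1.979 × 3.20 = 6.3 points unadjusted and 2.371 × 3.20 = 7.6 with Tukey. Both exceed 6.

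**7. Illustrations under assumptions that the protocol does not make.** The primary endpoint sets GBE/MST against both GBE and placebo. If GBE equals placebo and both comparisons must succeed under Tukey, power is 17%. If GBE alone has half the effect, so that GBE/MST exceeds GBE by 3 points (d = 0.2), that comparison has 15% power unadjusted and 8% with Tukey.

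**8. The 1% clause.** One percent of 15 is 0.15, not 6. Read instead as an SD of 15.15, it leaves d at 6/15.15 = 0.396. Neither reading yields the 6 points or the 44.

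**The case against.** Four points can be made for the plan.

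*The numbers may come from a recognisable calculation.* An effect of 0.4 entered as a point-biserial correlation, two-sided at 0.05, does give 44 (power 80.7%). But that 44 is a total, whereas the protocol uses it per group, and 6/15 is not a correlation. Likewise, a three-group ANOVA with f = 0.25 needs exactly 53 per group, 159 in total. The protocol does not mention f = 0.25, and it is a larger effect than 6 points at SD 15 (f of 0.16 to 0.19). These routes may explain where the figures came from; they do not justify them for the stated target. The match with d = 0.6 likewise shows only what 44 would suit: by the t-test it gives 79.5%, and the protocol states no 9-point target.

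*A baseline-adjusted analysis would be more powerful.* True, and the size depends on a correlation that the protocol does not give. For assumed baseline-to-24-week correlations of 0.5 to 0.8, adjusted power at 44 per group runs from 57% to 87% unadjusted for multiplicity, and from 42% to 77% with Tukey. The endpoint comparison as planned is not adjusted, and the calculation uses the raw SD.

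*SD 15 is a property of the scale, not an estimate for this sample.* Entry is limited to ages 20 to 64 with a MoCA-J of at least 26, so the SD here might differ. The protocol nevertheless bases its own calculation on 15.

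*The 46% and 31% assume exactly 44 completers.* This stands as a qualification. Between 42 and 53 completers the range is 44% to 53% (t-test) or 30% to 38% (Tukey), far below 80% throughout.

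**Conclusion.** The concern holds. On the protocol's own inputs, 44 per group is less than half of the 100 that a simple two-group comparison requires, and about a third of the 128 that a Tukey comparison requires. The 80% power claim for 6 points should read about 46% for a pairwise t-test, 36% to 47% for the omnibus ANOVA and 31% with Tukey.

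These figures rest on two-sided alpha 0.05, SD 15, 44 completers per group and the unadjusted endpoint comparison. A one-sided test would raise the pairwise t-test figure only to 58.6%. The conclusion does not depend on the 1% clause or on the illustrations in step 7. Because the error is in the inputs and result of a completed calculation, a separate statistical analysis plan could not reconcile them.

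**What to change.** Amend the Rationale paragraph and leave the sample size at 159:

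- State the 6-point target and SD 15 (d = 0.4) directly, and remove the 1% derivation. The 6 points must stay, because the restated power refers to them.
- Replace the 80% claim with the actual figures: with 44 completers per group, about 46% power for 6 points by a pairwise t-test (31% with Tukey), and 80% power for about 9.1 points (10.3 with Tukey). Say that these apply to the unadjusted endpoint score, two-sided at 0.05.
- If a baseline-adjusted comparison is made the primary analysis, give the power for that analysis with the assumed baseline-to-24-week correlation written out, and preferably a range.
- Add that a non-significant result does not exclude a 6-point benefit and that the confidence interval is to be used for interpretation.

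The cost is one reworded paragraph in an amendment and a less favourable stated power. No participants are added and no procedures change.

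### Enrolling 53 per group does not leave 44 after 20% dropout: it leaves about 42, and 44 would need 55 per group

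*Protocol*

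**What the plan says.** The Rationale under Sample size and rationale in the Protocol says that the calculation, with an effect size of 0.4, alpha 0.05 and 80% power, "yielded a sample size of 44 participants". The next sentence makes the attrition allowance: "Considering a dropout rate of 20%, 159 participants will be required (53 participants in each group"). The Sample size section repeats the total of 159 with the split "Control 53, GBE 53, GBE/MST 53", and the Abstract (Sample size and period) gives the same numbers.

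The inflation formula is not written out, and 44 is not labelled as a per-group number. Read as a per-group number it leads to 53 per group; read as a total it could not.

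**The concern.** A dropout rate is the fraction of enrolled participants who are lost, so the number to enrol is the target divided by the fraction retained. Multiplying the target by one plus the rate gives a smaller number, and the trial then falls short of its target when dropout runs exactly as planned.

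Completers are the right count here. Under Statistical methods, the primary comparison is of the total WMS-R score at the endpoint, by one-way ANOVA and Tukey's test. Under Methods (Schedule), the cognitive tests are given only at baseline and at 24 weeks. A participant who leaves before week 24 therefore has no endpoint score. At stake is whether the enrolment figure delivers the evaluable number on which the protocol rests its power.

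**Working it through.** **Inputs, all from the Protocol's Rationale and Sample size sections**

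- Target before attrition: 44, read as per group
- Dropout: 20%
- Enrolment: 53 per group in three equal groups, 159 in total
- For the power figures: a difference of 6 and a standard deviation of 15, so d = 6 / 15 = 0.4, with alpha 0.05

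**Step 1: reproduce the stated figure.** Target × (1 + rate) = 44 × 1.20 = 52.8, rounded up to 53. Then 3 × 53 = 159. Both stated numbers come out exactly.

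**Step 2: the number that keeps 44.** Target / (1 − rate) = 44 / 0.80 = 55 per group, and 3 × 55 = 165. Check: 55 × 0.80 = 44.0.

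**Step 3: what 53 delivers at 20% dropout.**

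| Enrolled per group | Total | Completers per group | Completers in total |
|---|---|---|---|
| 53 (as stated) | 159 | 53 × 0.80 = 42.4 | 159 × 0.80 = 127.2 |
| 55 | 165 | 55 × 0.80 = 44.0 | 165 × 0.80 = 132.0 |

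**Step 4: the dropout that 53 can absorb.** 1 − 44 / 53 = 0.170, or 17.0%.

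**Step 5: the chance of reaching the target.** Assume that each participant drops out independently with probability 0.20 (my assumption; the Protocol gives no model). The chance that a given group keeps at least 44 is then about 36% with 53 enrolled and 58% with 55. The chance that the trial keeps at least 132 is about 20% with 159 enrolled and 55% with 165.

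**Step 6: the cost in power.** The settings are d = 0.4, two-sided 5%, and noncentrality d × √(n/2) for n completers per group. The t-test uses 2n − 2 degrees of freedom. Tukey's test uses the studentised range for three groups with 3n − 3 degrees of freedom.

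| Completers per group | Two-group t-test | One Tukey pairwise comparison |
|---|---|---|
| 44 | 45.8% | 31.4% |
| 42 | 44.1% | 29.9% |

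The loss is 1.7 percentage points for the t-test and 1.5 for Tukey.

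**Step 7: whether a new base figure would remove the error.** It would not. Inflating by 1.20 and then losing 20% always leaves 1.20 × 0.80 = 0.96 of the target. Any replacement for 44 that was inflated the same way would fall 4% short, apart from rounding.

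**The case against.** The strongest reply is about weight, since the arithmetic itself is not in dispute.

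- **The method is inferred.** The Protocol writes out no inflation formula and does not call 44 a per-group or evaluable number. That is true, and the multiplication by 1.20 should be described as an inference. But it reproduces 53 and 159 exactly, and the shortfall does not depend on it: 80% of 53 is below 44 however 53 was reached.
- **The effect is small.** The gap is two completers per group and less than two points of power. The 20% has no stated source, so the difference between 17% and 20% lies within the uncertainty of the assumption. This stands as a comment on size. It does not make the printed figures consistent.
- **A larger problem sits upstream.** The figure of 44 does not follow from the stated inputs. A two-group comparison at d = 0.4 with 80% power needs about 99 per group two-sided, or 78 one-sided. If 0.4 was meant as Cohen's f in a three-group ANOVA, about 64 to 66 in total (22 per group) would be enough. On neither reading does the step from 42 to 44 decide whether the trial is adequately powered. This also stands. Step 7 shows, though, that correcting 44 would not correct the allowance.
- **The repair could mislead or cost more than it seems.** Moving to 55, or restating the dropout as 17%, could make 44 look like a verified requirement. Quoting power at 42 would put about 44% (d = 0.4, t-test) beside a claimed 80%, which is more than a slip in one sentence. Both cautions are fair and are carried into the fix.

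**Conclusion.** The point holds. At its own 20% dropout rate, the stated enrolment yields about 42 completers per group and not 44: 127 in total against 132. Enrolment is 2 per group, or 6 in total, below what the target and rate require, and 53 per group allows for 17.0% dropout.

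This rests on two readings: that 44 is a per-group number, which is needed to arrive at 53 per group, and that dropouts contribute no endpoint score, which follows from the two-visit testing schedule. The power figures also assume a two-sided test, because the Protocol does not state sidedness, and d = 0.4 as a standardised difference in means.

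The error is minor in effect and does not change the design or the analysis. It should still be corrected, because the protocol's sample size misses its own target. Correcting it would not establish 80% power.

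**What to change.** Choose one of these and amend the Rationale sentence:

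1. Keep 53 per group and state that this allows for 17% dropout while retaining 44 evaluable per group.
2. Keep 53 per group and 20% dropout, state that about 42 per group are then expected to be evaluable, and quote power at 42.
3. Keep both 44 and 20%, and enrol 55 per group (165 in total). The Sample size section and the Abstract then change as well.

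Options 1 and 2 add no participants. Option 1 costs one sentence and a slightly less favourable stated allowance. Option 2 is also short to write, but it cannot keep the 80% claim unless the base calculation is revisited: at d = 0.4 the t-test power at 42 is about 44%. Option 3 costs six more participants, and a change in participant number is listed as an amendment under Modification of the study protocol.

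Whichever is chosen, the derivation of 44 should be settled first. The Rationale should then label the base figure as per group and evaluable, and show the inflation as target / (1 − dropout rate), so that any new base figure is carried through correctly.
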